### **Safety Monitoring:**

Safety monitoring will be performed by an independent Data Safety Monitoring Committee comprised of researchers from Hanoi and individuals in Thai Nguyen with expertise in issues relevant to this study.

The committee will meet initially to review the protocol prior to submission to the Thai Nguyen Centre for Preventive Medicine IRB and before data collection begins, after which it will convene to review the study within one year of commencing enrollment and at least annually thereafter. Emergency meetings of the committee will be convened as needed.

At each meeting review of interim reports, the DSM Committee will review the following in a report prepared by a statistician external to the study team:

- Expected versus actual accrual rates
- Study retention rates, total and by study arm (unblinded)
- Study outcomes, as available, total and by study arm (unblinded)
- Numbers of adverse events and serious adverse events, by type, total and by study arms (unblinded)
- Any quality assurance or regulatory issues that occurred since the previous review
- Any actions or changes with respect to the study protocol.

Blind interim analyses of the data will be conducted halfway through the follow-up period, where virtually all participants will have provided 6-month behavioral interim endpoints. Interim reports will be prepared for the DSM Committee by an external statistician and will be presented to the protocol team blinded as to study arm, labeled as "A", "B", "C" "D".

Consideration will be given to stopping the study under each of the following scenarios.

- Increases in the overall number of drug use and risk behaviors for all study participants, as compared to baseline levels, that are statistically significant at the  $p < 0.001$  level.
- Differences in study outcomes between the control arm (receiving neither intervention) and any of the three study arms that are statistically significant at the  $p < 0.001$  level.

- Differences in the number of serious adverse events (calculated by collapsing all SAEs) between the control arm (receiving neither intervention) and any of the three study arms that are statistically significant at the  $p < 0.001$  level. SAEs include mortality, suicide, accidents and violence.

When considering whether to stop the study, the overall risks and benefits experience as of the interim analysis date will be weighted by the protocol team. The recommendation of the DSM Committee and opinion of the study sponsor will be given heavy weight.

Adverse events on which reports are collected by the study staff include not only physical harms such as mortality, suicide, accidents (traffic and other) and violence, but also social harms, such as arrest, incarceration, harassment by the police, being expelled from school or work, and instances of discrimination. Serious adverse events are based on the US Federal Drug Administration definition and are defined as events that result in death, are life-threatening, result in hospitalization or prolongation of existing hospitalization, a persistent or significant disability, a congenital abnormality or birth defect. Other injuries or medical events may be considered to be serious adverse events, when, in the opinion of a physician, they may jeopardize the participant and may require medical or surgical intervention to prevent one of the above outcomes. In our study, drug abuse or dependency alone in the absence of other adverse impact will not be considered to be an adverse event; however, patterns of drug use behavior will be analyzed. To our knowledge, there are no applicable Vietnamese laws for reporting suicide, physical abuse, sexual abuse or intentional HIV transmission.

AEs and SAEs reported to study staff will be reported to the local PI, [name] [name] within 24 hours orally or by email, and a completed written report of the event will be sent to the PI, [name] within 72 hours. A copy of the written report will also be sent to the NIDA project officer, the DSM Committee and IRBs within one week.

Reports of the DSM Committee meetings will be provided to the Thai Nguyen Centre for Preventive Medicine IRB and the Johns Hopkins Bloomberg School of Public Health IRB within 10 days.

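### The protocol team receives interim results by lettered arm and also weighs stopping, although two of the three stopping scenarios need the control arm identified and nobody is assigned to apply them or break the code

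*Protocol*

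**What the plan says.** All of the governing text is in the protocol's Safety Monitoring section.

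- **Committee's view.** A statistician outside the study team prepares the report. Its listed contents include "Study outcomes, as available, total and by study arm (unblinded"), and retention and adverse events are listed in the same way.
- **Team's view.** "Blind interim analyses of the data will be conducted halfway through the follow-up period", when nearly everyone has reached the 6-month behavioural endpoint. The reports written for the committee "will be presented to the protocol team blinded as to study arm", under the letters A to D.
- **Scenarios.** There are three, each at p < 0.001. The first pools everyone: "Increases in the overall number of drug use and risk behaviors for all study participants, as compared to baseline levels". The second is "Differences in study outcomes between the control arm (receiving neither intervention) and any of the three study arms". The third is "Differences in the number of serious adverse events (calculated by collapsing all SAEs) between the control arm (receiving neither intervention") and each of the other three arms.
- **Who weighs stopping.** When stopping is considered, "the overall risks and benefits experience as of the interim analysis date will be weighted by the protocol team". The committee's recommendation and the sponsor's opinion carry heavy weight, but neither is named as the decision-maker.

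**The concern.** The people running the trial are given comparative interim data under a letter code and are also asked to weigh stopping on criteria stated in terms of a named arm. The two roles pull against each other. To do the second properly, the team needs the information that the first withholds.

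The stake is operational bias. At the halfway look the stigma programmes are still running (Intervention Procedures has them continue for the full 24 months), tracing of missed visits is under way, and later index visits are still due. A team that sees how far the arms have separated on the primary behaviours could, without intending to, change programme intensity or follow-up effort. Letters are also thin protection here. The stigma programmes are delivered openly in assigned villages and announced by loudspeaker, and written reports of individual adverse events go to the Principal Investigator within 72 hours. If the lettered report carries serious adverse events by type and arm, someone who knows allocations could match counts to letters.

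**Working it through.** The protocol states no figure for this point, so the main check is to set the statements side by side. A short side calculation then shows how often the difficulty would arise.

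**1. Can a team that sees only A to D apply each scenario?**

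- Scenario 1 (all participants against baseline): yes. No arm identity is needed.
- Scenario 2 (control against each other arm, study outcomes): not from letters alone.
- Scenario 3 (control against each other arm, collapsed serious adverse events): not from letters alone.

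Four letters give 4 × 3 / 2 = 6 pairs, of which 3 include the control arm. If one pair crosses p < 0.001, the team cannot tell whether it is one of the 3 that count. Nor can it tell whether the better letter is an intervention arm (benefit) or the control arm (harm from an intervention). Weighing risks against benefits needs that direction. If no pair crosses, scenarios 2 and 3 are known not to be met and the code can stay closed.

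**2. How often would a control contrast cross?** One outcome, one look.

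*No true effect, four equal arms.* The bound is 3 × 0.001 = 0.3% for the control contrasts and 6 × 0.001 = 0.6% for all pairs. Simulation, with a crossing when two standardised arm means differ by more than 3.291 × √2, gives 0.29% and 0.56%.

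*Design alternative.* Sample Size and Power Calculations gives 85% power at alpha 0.05. Two-sidedness is assumed here. The standardised effect at full information is 1.960 + 1.036 = 2.996. At information fraction f, the chance that one contrast with that full power crosses p < 0.001 is Φ(2.996 × √f − 3.291). The protocol gives no f, so a range is shown:

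- f = 0.25: Φ(1.498 − 3.291) = 3.7%
- f = 0.50: Φ(2.119 − 3.291) = 12.1%
- f = 0.75: Φ(2.595 − 3.291) = 24.3%
- f = 1.00: Φ(2.996 − 3.291) = 38.4%

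A trigger is therefore plausible if the intervention works as designed, but not certain.

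**3. What does the team learn without any trigger?** If its copy shows outcomes by letter, it sees the size of every between-arm difference at the halfway look, whether or not a threshold is crossed. This exposure does not depend on the probabilities above.

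**4. What is still to come?** Index visits are at 3, 6, 12, 18 and 24 months. A participant who has reached only the 6-month visit has 3 of 5 follow-up visits left, and network members are retested for HIV only at month 24.

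**The case against.** The best defence is that the arrangement can be made to work. The committee holds unblinded data, an external statistician supplies it, and its recommendation carries heavy weight. Either could run the control-arm comparisons and advise without releasing the code. This stands, and it rules out several stronger readings that a reader might infer:

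- *The A to D blinding cannot hold.* Not supported. Unmasking is not inevitable, and if no pair of letters crosses, none is needed.
- *The statements on blinding and on stopping contradict each other.* Not supported. One says what each body sees, the other who weighs the result. What is missing is the step that joins them.
- *The committee's independence is lost.* Not supported. Its membership, data and freedom to recommend are unchanged. It is advisory, which is a different matter.
- *Every stopping scenario needs the control letter.* Not so. The pooled one does not.
- *Recruitment could be steered.* Hardly, since index enrolment is essentially finished when nearly everyone has 6-month data.
- *The HIV endpoint is exposed.* The interim is described in terms of behavioural data, and the network retest is at month 24.

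Two further points limit the concern. The protocol places assessment and intervention at separate sites so that assessors stay blinded, which protects the interviewer-collected outcomes. And it is an inference, though the natural one, that the team's copy shows outcomes by arm: a four-letter code has little purpose otherwise, and no text excludes it.

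What the defence does not answer is that the protocol assigns the workable route to nobody. It gives the weighing to the team, and is silent on who applies the comparisons and who may unmask.

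**Conclusion.** The point holds in a limited form. The protocol hands lettered comparative interim results to the team running the trial and makes that team the one that weighs stopping. Two of the three scenarios cannot be applied or interpreted from letters. When one of those two is triggered, the team must decide without knowing the arms or be unblinded, with no stated procedure for either.

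For one outcome at one look, a trigger has a chance of about 0.3% with no effect. It has about 4% to 38% for a contrast carrying the full design power, assuming a two-sided test and an information fraction between 0.25 and 1. The exposure of between-arm differences needs no trigger. It rests on the natural reading that the team's reports show results by letter. The size of any resulting bias cannot be calculated from the document. The matter should be corrected, because the protocol itself settles who sees interim data and who weighs stopping.

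**What to change.** Revise the Safety Monitoring section as follows:

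- Send outcome, retention and serious adverse event data by arm, lettered or not, only to the DSM Committee and the external statistician.
- Have the committee apply all three scenarios and send its recommendation to the sponsor and the protocol team.
- Give the protocol team pooled accrual, retention and safety totals only.
- Replace the sentence that has the protocol team weigh the interim risks and benefits with text consistent with this flow.
- State who may unmask, and when.

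No threshold changes, and both the committee and the external statistician already exist, so the direct cost is protocol wording. The real price is that the protocol team loses sight of coded interim results and gives up its lead role in weighing them.

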### **Confidentiality Assurances:**

#### *Certificate of Confidentiality/Letters of Commitment*

In Vietnam, there is no certificate of confidentiality. However, letters of commitment from authorities have been obtained that assure no breaches in confidentiality.

#### *Data Security*

All participants will receive an identification number (PID) and this number will be used for all interviews. No other information that would disclose the participant's identity will be found on any interview. Data will be kept without serostatus identification in locked cabinets at the Center for Preventive Medicine in Thai Nguyen. Only the consent form, tracker form and tracker computer will link the participant's name to the identification number. To maintain contact with participants, we will use a computerized tracking system as described in the Study Procedures section. In addition, interviewing and office staff will sign a confidentiality pledge prior to having contact with participants.

We will take steps to maintain strict confidentiality of information on participants' HIV status. To ensure that the HIV serostatus of IDUs will not be disclosed by virtue of their participation in the study, we are not limiting enrollment to HIV-positive individuals. As part of Phase I, we will conduct focus groups among men

and women in the community, and HIV-serostatus will not be an eligibility criterion for this component of the study. Furthermore, our consent forms do not divulge that HIV status is an eligibility criterion for the intervention component. Although informed consent forms should disclose all eligibility criteria, however given the potential disclosure of sensitive information contained in the consent form (e.g., if a third party deliberately or inadvertently obtained the participant's copy of the consent form,) it would constitute a breach of confidentiality; therefore we are omitting this information from the consent form.

Our project sites are currently located in primary health centers (not HIV, VCT, infectious diseases or TB ward) to ensure that participation in our study does not disclose participants HIV and drug using status. And, our study name will be selected by local staff and will not contain any information about IDUs or HIV.

#### *Who Will Have Access to the Data*

To ensure confidentiality, electronic data will be saved on password-protected secure computers. Access to security passwords will be given only to the PI and Field Director, [name] [name] at CPM. Personal identifiers will not be stored in the data set and all computers will be protected by anti-virus software. Raw data files will be destroyed in the field setting by shredding after one year from being electronically coded. Tapes of the qualitative interviews and focus group discussions will be destroyed within one year of being transcribed electronically by crushing and cutting the tapes. Blood samples will be incinerated after 5 years of storage in lab facilities.

#### **Collaborative Agreements:**

The study will be conducted in collaboration with the Thai Nguyen Center for Preventive Medicine (CPM), based on Memorandums of Understanding between JHU and the CPM. The local IRB is reviewing the research plan and consent forms. The approval letter will be forwarded to the JHU IRB when it is available.

The Thai Nguyen IRB is registered with the OHRP and has been granted Federalwide Assurance (IRB00004109; FWA00007138).

